## Abstract

**Introduction:**

Pulmonary rehabilitation (PR), an exercise and education programme for people with chronic lung disease, aims to improve exercise capacity, breathlessness and quality of life. Most evidence to support PR is from trials that use specialist exercise equipment, for example, treadmills (PR-gym). However, a significant proportion of programmes do not have access to specialist equipment with training completed with minimal exercise equipment (PR-min). There is a paucity of robust literature examining the efficacy of supervised, centre-based PR-min. We aim to determine whether an 8-week supervised, centre-based PR-min programme is non-inferior to a standard 8-week supervised, centre-based PR-gym programme in terms of exercise capacity and health outcomes for patients with chronic lung disease.

**Methods and analysis:**

Parallel, two-group, assessor-blinded and statistician-blinded, non-inferiority randomised trial. 436 participants will be randomised using minimisation at the individual level with a 1:1 allocation to PR-min (intervention) or PR-gym (control). Assessment will take place pre-PR (visit 1), post-PR (visit 2) and 12 months following visit 1 (visit 3). Exercise capacity (incremental shuttle walk test), dyspnoea (Chronic Respiratory Questionnaire (CRQ)-Dyspnoea), health-related quality of life (CRQ), frailty (Short Physical Performance Battery), muscle strength (isometric quadriceps maximum voluntary contraction), patient satisfaction (Global Rating of Change Questionnaire), health economic as well as safety and trial process data will be measured. The primary outcome is change in exercise capacity between visit 1 and visit 2. Two sample t-tests on an intention to treat basis will be used to estimate the difference in mean primary and secondary outcomes between patients randomised to PR-gym and PR-min.

**Ethics and dissemination:**

London-Camden and Kings Cross Research Ethics Committee and Health Research Authority have approved the study (18/LO/0315). Results will be submitted for publication in peer-reviewed journals, presented at international conferences, disseminated through social media, patient and public routes and directly shared with stakeholders.

**Trial registration number:**

ISRCTN16196765.

Strengths and limitations of this studyThis is a parallel, two-group, assessor-blinded and statistician-blinded, non-inferiority randomised trial to assess the primary and secondary outcome measures.The pulmonary rehabilitation intervention is delivered according to national guidelines: British Thoracic Society Guideline on Pulmonary Rehabilitation in Adults.The study includes a 12-month follow-up period to evaluate the long-term effect of the intervention.The study includes a health-economic analysis which aims to understand relative cost-effectiveness which may have implications for NHS commissioning.This is a single-centre study based in northwest London and findings may not be applicable to other populations in different locations.

## Introduction

### Background and rationale

Pulmonary rehabilitation (PR), an evidence-based exercise and education programme, is widely accepted as a cornerstone of management for people with chronic obstructive pulmonary disease (COPD) and other chronic respiratory disorders.^1^ The most recent Cochrane review, comprising 65 randomised controlled trials (n=3822), stated that no further trials comparing PR and standard care in patient with COPD were necessary as the evidence supporting the benefits of PR on exercise capacity and health-related quality of life were conclusive.^2^

The majority of evidence to support PR has come from trials conducted in hospital or rehabilitation centres that use specialist exercise equipment such as treadmills, cycle ergometers and weights machines (PR-gym).^2^ However, in clinical practice, supply does not meet demand, and routine access to specialist equipment may not be feasible.^3^ For example, the 2015 Royal College of Physicians National Audit identified that PR services in England and Wales received 68 000 referrals in 2014 out of an estimated 446 000 eligible patients with COPD.^3^ Furthermore, 82% of patients enrolled in a PR programme in England and Wales in 2017 were hosted in a community site such as a community centre or church hall, of which 61% most likely did not exercise using specialist equipment.^4^ Accordingly, exercise training at these sites, although supervised by PR professionals, was completed with minimal equipment (PR-min), typically using portable equipment such as free weights, elastic resistance bands (eg, Theraband), walking courses and bodyweight resistance exercises.^3^

Apart from improving accessibility, it has been argued that PR-min may have other advantages over PR-gym. Exercise-training using minimal equipment may better reflect activities of daily-living than training using specialist equipment and therefore be easier to replicate and maintain at home following discharge from PR. However, it may be more difficult to prescribe and progress exercise, particularly resistance exercise, without the use of specialist equipment.

A systematic review, conducted by Alison and colleagues, identified eight randomised controlled trials that compared outcomes following exercise interventions completed with minimal equipment to usual care without an exercise intervention in patients with COPD.^5^ The results were conflicting for exercise outcomes. In four studies (n=182) where the 6 min walk test was used as the primary outcome measure of exercise capacity, the pooled effect showed a mean (95% CI) between-group difference of 40 (13 to 67) m favouring the intervention group.^5^ Conversely, in the other four studies (n=389) that used the incremental shuttle walk test (ISW), there was no significant mean (95% CI) between-group difference: 21 (−9 to 51) m.^5^ For health-related quality of life, results were similarly conflicting.^5^ Whereas in the four studies that used the St. George’s Respiratory Questionnaire there was a sizeable difference between the intervention and control groups (mean (95% CI): −7 (−12 to −3)), the mean between-group difference of the Chronic Respiratory Questionnaire dyspnoea (CRQ-D) and fatigue domains (CRQ-F) did not reach the minimum clinically important difference (MCID) in three other studies.^5^ Only one of the eight studies measured muscle strength but results were reported descriptively with no statistical testing.^5^ Furthermore, only one of the eight studies would fulfil the British Thoracic Society (BTS) guidelines definition of PR,^1^ with seven studies not offering any education component.^5^

To our knowledge, no trial has compared supervised centre-based PR using minimal and specialist equipment. A previous National Institute for Health Research Health Technology Assessment-funded randomised 2×2 trial compared PR undertaken in community venues with PR undertaken in a hospital venue, in 240 patients with COPD.^6^ Participants were block randomised (hospital n=129; community n=111). Both groups received two times a week PR for 6 weeks with the exercise training protocol identical in both venues. Importantly, neither community nor hospital sites had access to specialist exercise equipment. Patients in both groups improved their walking distance, exceeding the MCID of the endurance shuttle walk test, and there were similar improvements in health-related quality of life.^6^ Although the results support the conclusion that the efficacy of PR-min is not influenced by hospital or community locations, this study did not address whether PR-min is non-inferior to ‘gold standard’ PR-gymOur group recently conducted an observational cohort study to compare if an 8 week supervised, centre-based PR-min programme was non-inferior to PR-gym in terms of core PR outcomes in patients with COPD.^7^ Using propensity score matching, 318 consecutive patients undergoing PR-min were compared 1:1 with a control group of 318 patients who underwent PR-gym. Similar short-term improvements in exercise capacity and health-related quality of life were observed in both groups (mean (95% CI) difference: ISW: 3 (−16 to 9) m; CRQ-total: 0.9 (−2.7 to 4.5)). Furthermore, the 95% CI between-group differences for these outcomes did not cross the predefined non-inferiority margins. These data suggest that PR-min is non-inferior to PR-gym with regard to short-term improvements in exercise capacity and health-related quality of life. However, this study was not randomised, only included short-term outcomes and no attempt was made to estimate costs. A randomised controlled trial with more varied outcome measures (such as lower limb muscle strength), longer follow-up and a health economic analysis, is required to confirm these findings.

The aims of the research are to determine whether an 8-week outpatient supervised PR-min programme is non-inferior to a standard 8-week outpatient supervised PR-gym programme in terms of health benefits for patients with chronic respiratory disease.

The primary objective is to determine whether PR-min is non-inferior to PR-gym regarding change in exercise capacity measured using ISW^8^ distance from baseline (visit 1) to post-PR assessment at 8 weeks (visit 2).

The secondary objectives are to: (1) determine whether PR-min is non-inferior to PR-gym regarding changes breathlessness (CRQ-D), health-related quality of life (CRQ) and quadriceps strength (isometric quadriceps maximum voluntary contraction) from baseline (visit 1) to post-PR assessment at 8 weeks (visit 2) and from baseline (visit 1) to 12 months after the baseline assessment (visit 3); (2) evaluate the trial process by recording the participant recruitment and retention, participant uptake of PR, PR attendance, PR completion, reasons for PR non-completion and participant satisfaction in each arm of the study, at the appropriate stage of the trial; (3) estimate the cost and cost-effectiveness during the trial period.

## Methods and analysis

### Ethical approval

This study has been approved by the Health Research Authority and London Camden and Kings Cross Research Ethics Committee (reference 18/LO/0315). All participants will provide written informed consent.

### Study design

This is a parallel, two-group, assessor-blinded and statistician-blinded, non-inferiority, randomised trial. Participants will be randomised at the individual level with a 1:1 allocation to either PR-min or PR-gym. Both interventions will comprise two supervised sessions per week for 8 weeks delivered by the same team. Outcome measures will be recorded at baseline assessment for PR (visit 1), following PR at 8 weeks (visit 2) and at 12 months after visit 1 (visit 3). The study schema is outlined in figure 1.

**Figure 1 F1:**
[figure not shown]
Study schema. CRQ-D, Chronic Respiratory Questionnaire-Dyspnoea; CRQ-T, Chronic Respiratory Questionnaire-Total Score; CVS, Cardiovascular Disease; ISW, Incremental Shuttle Walk Test; KCTU, King’s Clinical Trials Unit; MRC, Medical Research Council; PR, Pulmonary Rehabilitation; QMVC, Quadriceps Maximum Voluntary Contraction.

### Study population

Potential participants will be people referred to Harefield Pulmonary Rehabilitation Unit, Royal Brompton and Harefield Clinical Group, UK who meet the following inclusion criteria (1) adults >18 years of age; (2) physician diagnosis of stable chronic respiratory disease, typically COPD, interstitial lung disease, bronchiectasis, chronic asthma or chest wall disease; (3) referred for PR in line with BTS guidelines (ie, ambulatory—can walk ≥5 m, functional impairment related to breathlessness, typically Medical Research Council dyspnoea score ≥2); (4) able to communicate verbally and respond to questions in written English. Potential participants will be excluded if they have (1) any contraindication to moderate intensity physical exercise, for example, unstable cardiovascular disease; (2) progressive cancer or neurological disorder with an expected life expectancy less than 12 months; (3) completed PR within previous 12 months and/or (4) are unable to provide informed consent.

### Consent

Informed consent will be obtained by the nominated researchers as recorded in the Sponsor’s Delegation of Responsibilities Log. All individuals taking informed consent will have received consent training. All participants will provide written consent. Consent to enter this study will be obtained after a full account has been provided of its nature, purpose, risks, burdens and potential benefits, and the patient has had the opportunity to deliberate. The patient will be allowed to specify the time they wish to spend deliberating, usually up to 24 hours. The Investigator or designee will explain that the patients are under no obligation to enter the study and that they can withdraw at any time during the study, without having to give a reason. At each visit, the participant’s willingness to continue in the study will be ascertained and documented in the research notes. A copy of the consent form is in the online supplemental file.

10.1136/bmjopen-2020-047524.supp1Supplementary data

### Screening and recruitment

Following clinical referral, but prior to pre-PR assessment, potential participants will be screened by a member of the PR team for eligibility to the study. The potential participant will be approached by telephone and provided with a participant information sheet. A member of the research team will obtain informed consent following the pre-PR assessment.

### Randomisation, allocation and blinding procedures

Consenting participants will be randomised at the individual level with a 1:1 allocation, using an independent web-based system provided by the United Kingdom Clinical Research Collaboration registered King’s Clinical Trials Unit (KCTU), to receive either ‘usual care’ (PR-gym) or intervention (PR-min).

Randomisation by minimisation will ensure that participant characteristics are balanced between the groups with respect to previous completion of PR (yes/no), multiple deprivation index (most deprived quintile of index: yes/no^9^ and frailty status (Short Physical Performance Battery score <10/≥10.^10^ A proportion of patients will be entered initially using simple randomisation in order to create a level of initial imbalance and the minimisation algorithm will maintain a level of randomness in order to preserve prerandomisation allocation concealment. Once randomised, the system will automatically generate a full audit trail of the process and send email to relevant investigators in a blinded or unblinded format, depending on their role. For each arm, participants will be provided with a choice of three sites in northwest London to undertake PR.

Owing to the nature of the interventions, participants and providers of the intervention will not be blinded. However postrehabilitation assessments will be performed by a researcher blinded to group allocation and not involved in the delivery of either intervention arm. The trial statistician will also be blinded to group allocation.

### Study intervention

#### PR-gym (control group)

The control intervention will be current gold-standard clinical practice. PR-gym will comprise an 8-week outpatient exercise and multidisciplinary self-management education programme, with two supervised and at least one additional home session each week, and delivered according to the BTS Quality Standards for PR.^11^ Supervising staff will comprise specialist respiratory therapists with a minimum of 2 years’ experience in PR. Available equipment will include treadmills, cycle ergometers, cross-trainers, specialist lower limb resistance equipment (eg, leg press, knee extension). Each supervised session will consist of 1 hour of exercise (at least 30 min aerobic exercise) and 45 min of education.

Initial walking speed prescription on the treadmill will be 80% of predicted peak oxygen consumption based on baseline ISW performance,^8^ while initial endurance cycling will be initially set to achieve level 3 to 4 on the Borg CR-10 Dyspnoea Scale with the aim of patients completing 10 min of continuous training. Lower limb resistance training will comprise two sets of 10 leg press repetitions on specialist resistance equipment performed with an initial training load of 60% one-repetition maximum. Similarly, two sets of 10 bilateral knee extension repetitions will be performed on specialist resistance equipment at an initial training load of 60% one-repetition maximum. This will be supplemented with sit-to-stand sets, plus knee lifts/extension and hip abduction with appropriate ankle weights up to 10 kg. Upper limb resistance training will comprise biceps curls, shoulder press and upright row with free weights or Therabands (red to black). Exercise training will be individualised and regularly progressed (duration and/or intensity) according to standard operating procedures, with targets reviewed at each session. Education will be delivered by a multidisciplinary team with topics chosen to develop patients’ understanding and holistic management of their disease. Further detail on the education programme and safety measures for the rehabilitation programme are provided in the online supplemental file.

#### PR-min (Intervention group)

PR-min will also comprise an 8-week outpatient exercise and multidisciplinary self-management education programme, with two supervised and at least one additional home session each week, and delivered according to the BTS Quality Standards for PR.^11^ As for PR-gym, supervising staff will comprise specialist respiratory therapists with at least 2 years’ experience of in PR. There will be no access to treadmills, cycle ergometers or specialist resistance equipment. Available exercise equipment will include walking circuit, portable steppers, portable pedals, hand and ankle weights (up to 5 kg), and Therabands (red to black). Each supervised session will consist of 1 hour of exercise (at least 30 min aerobic exercise) and 45 min of education.

Initial walking speed prescription will be 80% of predicted peak oxygen consumption based on baseline ISW performance. Participants will be provided with a stopwatch and given time targets to complete a walking course of known distance. Although the resistance of the portable steppers and pedals can be manually adjusted, this cannot be objectively quantified. Initial prescription will be set at ‘level 1’ but individually adjusted to find an intensity where patients can complete 10 min of continuous training with a target modified Borg breathless score of 3–4 and a Borg rating of Perceived Exertion of 13–15 (on a scale of 6–20). Resistance training will include functional activities such as sit-to-stand and step-ups as well as Theraband based exercises such as sitting knee extension, leg press and hip flexion as well as standing hip extension, squats, chest press and lateral raise. Progression will be through the use of hand/ankle weights and increasing resistant Therabands (from red to black). Exercise training will be individualised and regularly progressed (either in duration or intensity) with targets reviewed at each supervised session. Education will be delivered by a multidisciplinary team as per PR-gym (online supplemental file). Information on safety measures for the rehabilitation programme is provided in the online supplemental file.

### Study outcome measures

A list of the scheduled outcomes is outlined in table 1 and described in detail in the online supplemental file.

**Table 1 T1:** Study outcome measures

	Visit 1	Visit 2	Visit 3
Primary outcome measure: exercise capacity (incremental shuttle walk test)	X	X	X
Spirometry	X		X
Frailty (Short Physical Performance Battery)	X	X	X
Dyspnoea (Chronic Respiratory Questionnaire-Dyspnoea domain)	X	X	X
Health-related quality of life (Chronic Respiratory Questionnaire)	X	X	X
Muscle strength (Isometric Quadriceps Maximum Voluntary Contraction)	X	X	X
Patient satisfaction (Global Rating of Change Questionnaire)		X	
Health-economic evaluation (Modified Client Service Receipt Inventory Scale, Euro-Qol-5 Dimensions-5 Levels, NHS Digital—after visit 3 only)	X	X	X
Safety and trial process evaluation	X	X	X

### Sample size calculation

Previous audits of Harefield PR Unit have shown that in participants undergoing PR-gym achieve a mean (SD) change in ISW of 58 (67) m. The null hypothesis is that PR-min is inferior to the standard treatment PR-gym. The alternative hypothesis is that PR-min is not inferior to PR-gym. The non-inferiority margin will be defined as half the known MCID using the fixed-margin method with a preserved effect of 50% as recommended by previous guidance, including from the United States Food and Drug Administration.^12 13^ The MCID of the ISW is 47.5 m,^14^ and therefore 24 m will be considered the non-inferiority margin. If there is truly no difference between PR-min and PR-gym, then a minimum of 246 patients (123 in each group) is required to be 80% sure that the lower limit of a one-sided 97.5% CI (or equivalently a 95% two-sided CI) will be above the non-inferiority limit of −24 m. Based on audit data, we anticipate 32% dropout from PR (12% from assessment to starting PR and 20% from starting PR to completing PR). Taking into account dropout, the original minimum sample size required for analysis was 362 patients (181 patients per group). However, owing to the impact of the COVID-19 pandemic on the study (described in the Amendment section), the study sample size was increased by a further 74–436 (218 patients per group).

### Statistical analysis

For baseline data, continuous and categorical variables will be summarised with descriptive statistics. No significance testing will be carried out. The outcome measures will be described by trial arm and at visits 1, 2 and 3 using descriptive statistics.

The main statistical analyses will estimate the difference in mean primary and secondary outcomes between patients randomised to PR-gym and PR-min by intention to treat principle from visit 1 to visit 2 (8 weeks following visit 1) and visit 1 to visit 3 (12 months following visit 1). Group difference estimates and associated one-sided 97.5% CI will be reported. The group differences will be compared using one-sided two independent sample t-test or non-parametric equivalent. The significance level is set at one-sided significance level of 0.025.

Regarding missing data, the number of baseline variables with complete data will be reported and the primary and secondary outcomes will be analysed as per the recommendations of White *et al*.^15^ Missing postrandomisation assessments will be dealt with using an appropriate method of imputation, depending on the missing mechanism.

Adherence is defined as the number of supervised sessions the participant attends irrespective of the assigned intervention (maximum 16). This will be recorded in both intervention arms. As a dichotomous indicator with eight as the cut-off. The following variables will be recorded in a 3×2 table according to allocated intervention: (1) compliers always receive the allocated treatment; (2) complete defiers do the opposite of the allocated treatment, that is, attend no sessions in allocated treatment; (3) partial defiers are all others not falling in the above groups. Dropout cause will be recorded using the MORECARE classification of reason for attrition.^16^

In addition to the primary intention-to-treat analysis, the effect of actually receiving treatment as defined in the protocol will also be estimated. If non-compliance rate with PR sessions is >10%, a Complier-Average Causal-Effect (CACE) will be estimated.^17^ The following sensitivity analyses are planned: (1) per protocol; (2) including only those in the upper quartile for baseline ISW; (3) complete case; (4) complier Average Causal Effects (CACE) analysis^17^ and (5) primary diagnosis of COPD; (6) a generalised estimating equation-based analysis to estimate the treatment effects, adjusting for imbalance if the group difference in the percentage of smokers, participants age <70 years, or females is greater than 20% at baseline.

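### The primary analysis leaves out baseline ISW and the three minimisation factors as covariates, and its rank-test alternative does not target the mean difference on which the 24 m margin is set

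*Protocol article*

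**What the plan says.** **Outcome and test.** The abstract states: "The primary outcome is change in exercise capacity between visit 1 and visit 2". For the method it says "Two sample t-tests on an intention to treat basis will be used to estimate the difference in mean primary and secondary outcomes" and mentions no alternative. The Statistical analysis section adds one: "The group differences will be compared using one-sided two independent sample t-test or non-parametric equivalent". It does not name the alternative test or say when it would be used.

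**Target and interval.** The same section says "The main statistical analyses will estimate the difference in mean primary and secondary outcomes" and "Group difference estimates and associated one-sided 97.5% CI will be reported", and "The significance level is set at one-sided significance level of 0.025". The Sample size calculation section sets the limit at −24 m and takes 67 m as the SD of change.

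**Allocation.** The randomisation section says "Randomisation by minimisation will ensure that participant characteristics are balanced between the groups with respect to previous completion of PR (yes/no", and adds most deprived quintile (yes/no) and Short Physical Performance Battery (SPPB) score below 10 or not.

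**Adjustment.** The only adjusted model is the sixth sensitivity analysis, a generalised estimating equation. It adjusts only if the arms differ by more than 20% in smoking, age under 70 or female sex. It names neither baseline ISW nor a minimisation factor. Baseline ISW otherwise serves only to select the upper-quartile subset for another sensitivity analysis.

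**The concern.** There are two separate points.

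1. **Unadjusted analysis after minimisation.** Minimisation makes the arms alike on factors thought to matter. An unadjusted t-test still counts the variation due to those factors as error, so its standard error is larger than the design warrants. A change score assumes a slope of exactly 1 on baseline ISW. If change depends on baseline, that dependence stays in the residual, as does any chance imbalance in baseline ISW, which is not a minimisation factor. The trial is planned at 80% power with 32% dropout, so lost precision matters.

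2. **The rank option.** The margin and the sample size are defined on a mean difference in metres. A rank test in its default form has zero difference as its null and gives no mean difference. With no trigger stated, the choice of primary test could depend on how the data look.

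**Working it through.** **Inputs from the protocol article.** SD of change 67 m; margin 24 m; true difference 0; one-sided alpha 0.025; power 80%; dropout 32%.

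**Step 1: reproduce the stated figures.**
- n per arm = 2 × 67² × (1.960 + 0.842)² / 24² = 122.3, so 123; total 246.
- 246 / (1 − 0.32) = 361.8, so 362; 362 + 74 = 436.
- Standard error at 123 per arm = 67 × √(2/123) = 8.54 m. Half-width = 1.96 × 8.54 = 16.7 m. Power = Φ(24/8.54 − 1.96) = 80.2% (79.9% with the noncentral t).

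The figures agree with the planned t-test.

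**Step 2: effect of adjustment.** Let R² be the share of variance in change explained by baseline ISW and the three factors. The documents give no value, so 0.05 to 0.25 is an assumption. The residual SD is 67 × √(1 − R²).

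The gain depends on where the R² comes from.
- *Column A:* the unadjusted test when the covariates are not balanced by design, with power Φ(24/8.54 − 1.96).
- *Column B:* the unadjusted test when all of R² comes from factors that minimisation balances perfectly. The estimate then already has the smaller true standard error SE_adj, but the test still uses 8.54, so power is Φ((24 − 16.745)/SE_adj).

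| R² | Residual SD (m) | SE_adj (m) | Half-width (m) | Adjusted power | A | B | Gain (points) |
|---|---|---|---|---|---|---|---|
| 0.05 | 65.3 | 8.33 | 16.3 | 82.2% | 80.2% | 80.8% | 1.4 to 2.0 |
| 0.10 | 63.6 | 8.11 | 15.9 | 84.2% | 80.2% | 81.5% | 2.7 to 4.0 |
| 0.20 | 59.9 | 7.64 | 15.0 | 88.1% | 80.2% | 82.9% | 5.2 to 7.9 |
| 0.25 | 58.0 | 7.40 | 14.5 | 90.0% | 80.2% | 83.7% | 6.3 to 9.8 |

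A simulation of 3,000 trials of 246 patients points the same way. It assumed factor prevalences of 30%, 20% and 50%, an 80% biased coin and 20 simple-randomised starts. Unadjusted against adjusted power was 78.4% against 80.1% at R² 0.05, 81.1% against 83.9% at 0.10, and 82.6% against 88.4% at 0.20.

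**Step 3: type I error of the unadjusted test.** Under perfect balance it is 1 − Φ(1.96/√(1 − R²)): 0.022, 0.019 and 0.014 at R² 0.05, 0.10 and 0.20. The simulation gave 0.022, 0.024 and 0.012 (Monte Carlo error about 0.003). None exceeds 0.025.

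**Step 4: the rank option** (simulation, 123 per arm).
- *Unshifted Mann–Whitney, arms equal:* rejects in about 2.4% of trials. It tests superiority to zero, so it cannot show non-inferiority.
- *Mann–Whitney after adding 24 m to PR-min* (the test that matches a Hodges–Lehmann interval), normal data, pure location shift: type I error about 0.024, power about 77%.
- *Same shifted test when the arms differ in shape:* in an illustration where 20% of PR-min patients do 120 m worse, the mean difference is 0.20 × (−120) = −24 m, exactly the margin. The shifted test declared non-inferiority in about 5% of trials, against 2% to 3% for the Welch t-test.

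**The case against.** **No validity error is shown.** This stands. An over-large standard error makes non-inferiority harder to claim, and the sample size matches the planned test. A reader might infer that omitting the factors makes the result unsafe or the sample size wrong; Steps 1 and 3 show neither.

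**Baseline ISW is not ignored.** This also stands. It is subtracted; what is lost is any remaining slope of change on baseline, for which the documents give no figure.

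**The non-inferiority rule survives the rank wording.** Largely right. A reader might infer that a rank test can never be read against −24 m, or that the rule could not then be applied. The documents do not support this. They commit, in sentences separate from the test, to a difference in means with a one-sided 97.5% CI, and nothing says that the alternative replaces that interval. A shifted rank test or Hodges–Lehmann interval is also in metres. What remains is that these target a location shift, which equals the mean difference only if the arms have the same shape.

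**Test and trigger are details for the analysis plan.** Partly fair, since that plan is not shown. But the article itself fixes the unadjusted test and offers the alternative, and its abstract omits the alternative.

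**The gain is assumed and easily overstated.** Fair. A formula that ignores minimisation gives column A; where the factors are already balanced, column B is the right comparator.

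**Conclusion.** The point holds as a matter of efficiency and of an unsettled primary method. The primary analysis is unadjusted, no stated analysis uses the minimisation factors, and baseline ISW enters only by subtraction.

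If R² is 0.05 to 0.25, adjustment narrows the half-width by about 0.4 to 2.2 m. The power gain is at most about 4 points for R² up to 0.10 (2 to 3 in the simulation with balanced factors). It is roughly 5 to 8 points at R² 0.20, with the upper end applying only where the explained variance comes from covariates that minimisation has not balanced. R², the factor prevalences and the minimisation settings are all assumptions. The cited missing-data recommendation could not be checked for covariates.

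The rank wording needs clarifying because its target differs from the one the margin was set on. It does not make the trial's decision rule unusable.

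**What to change.** - **Primary analysis:** a linear model of visit 2 ISW (or change) on arm, baseline ISW, previous PR, deprivation quintile (yes/no) and SPPB category. Read the lower one-sided 97.5% limit for the arm effect against −24 m.
- **Secondary outcomes:** the same form where a baseline value exists. It cannot apply to the Global Rating of Change, which Table 1 schedules at visit 2 only.
- **Rank option:** for the primary outcome, replace it with a bootstrap or robust-standard-error interval for the mean difference.
- **Sensitivity analyses:** keep the unadjusted t-test, and any rank analysis, here. Bring the abstract and the Statistical analysis section into line.

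**Cost.** There is no new data collection: ISW and SPPB are measured at visit 1 and the allocation factors are needed to randomise. The required sample size does not rise. Recruitment began in October 2018 and the t-test is published, so this changes a pre-specified primary analysis. It should be documented and dated before unblinding.
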